## Abstract

**Background:**

The purpose of this study is to verify the improvement of remote qigong intervention on the quality of life and physical fitness of breast cancer patients after surgery by means of a randomized controlled trial and to compare it with the conventional exercise combination of aerobic exercise and resistance training.

**Methods/design:**

The research approach applied in this study is a randomized controlled trial. After completing the baseline questionnaire and physical fitness test, participants were randomly assigned to either the qigong group or the combined exercise rehabilitation group. Patients in the qigong group performed Qigong-Baduanjin twice a week for 30 min each time under remote guidance and practiced Baduanjin by themselves at other times. Patients in the combined exercise rehabilitation group were given resistance training twice a week for 30 min under remote guidance, and walking the rest of the time. At the end of the 12-week intervention, outcomes testing and data collection were carried out. The primary outcomes are quality of life, measured using the Medical Outcomes Study 36-Item Short-Form Health Survey (SF-36), and the Functional Assessment of Cancer Therapy-Breast (FATC-B). The secondary outcomes include cardiopulmonary endurance, upper limb strength, lower limb strength, and skinfold thickness.

**Discussion:**

The importance of postoperative exercise rehabilitation for breast cancer has been gradually accepted by more and more doctors and patients, but further research and development of simple and practical means of exercise rehabilitation are necessary. Remote qigong intervention for breast cancer patients via the Internet will be a great alternative.

**Trial registration:**

Chinese Clinical Trial Registry ChiCTR1900027989. Registered on December 7, 2019.

## Background

Breast cancer is the most common malignant tumor in women worldwide and the second leading cause of cancer death in women. In recent years, with the continuous improvement of medical technology, the number of breast cancer survivors continues to grow. However, postoperative breast cancer patients often suffer from complications such as pain, limited upper limb activity, fatigue, obesity, premature menopause, and lymphedema, which seriously reduces the quality of life of patients. Therefore, more and more attention has been paid to the rehabilitation of postoperative breast cancer patients [1, 2].

Previous studies have revealed that exercise intervention will reduce mortality risk in breast cancer patients and improve the quality of life, physical function, and social cognition of survivors after breast cancer surgery [3, 4], and has a certain healing effect on patients after breast cancer surgery [5, 6]. Nevertheless, traditional exercise intervention failed to attract participation and improve the rehabilitation effect because of distance, time consumption, money, transportation, and so on. With the development of modern network technology, remote intervention has become possible. Studies have verified the effectiveness of remote intervention for breast cancer patients after surgery.

Qigong is a form of exercise focusing on physical activity, breathing, and psychological regulation, and a psychosomatic therapy [7]. Previous studies have shown that qigong exercise can improve the fatigue perception and sleep quality of breast cancer patients undergoing postoperative chemotherapy, reduce the risk of lymphedema, and improve their quality of life and physical fitness [8]. However, there is still a lack of research on the effect of remote exercise qigong intervention on postoperative recovery of breast cancer patients and it is also unclear whether qigong intervention is more advantageous than the conventional intervention combination of aerobic exercise and resistance exercise. This study is intended to verify the effect of long-range qigong intervention on the improvement of quality of life and physical fitness in breast cancer patients by means of randomized controlled trials and to compare it with conventional exercise intervention methods.

### Objectives

To explore whether Internet remote intervention can be used as a simple and practical means of exercise rehabilitation through experimentsTo explore whether remote qigong intervention can improve the quality of life and physical quality of breast cancer patients

## Design and methods

### Design

This study is an RCT with an intervention time of 12 weeks. Trial participants will be recruited starting in February 2019 and the data will be analyzed after the sample size is achieved according to the study design. The flow chart of the study design is shown in Fig. 1.

**Fig. 1 Fig1:**
[figure not shown]
The flow chart of the trial design

### Subject recruitment

#### Inclusion criteria

Female breast cancer patients (stage I–III), aged over 18 yearsNo recurrence and no tumor metastasisRadiotherapy/chemotherapy was completed within 4–18 months after surgery

#### Exclusion criteria

Language disorders or communication disordersSerious exercise contraindications, such as cardiovascular or articular problemsHaving any other serious illness or mental illnessHaving received qigong exercise or other planned exercisesUnable to use the Internet by oneself or with the help of others

#### Drop out criteria

There were recurrence and tumor metastasis during the interventionSubjects who cannot insist on receiving intervention for some reason

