### Implementation

After completing the baseline survey and physical fitness test, the computer random table generated by SPSS16.0 software was used for randomization. The eligible patients were randomly divided into an experimental group and control group, with a ratio of 1:1.

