### Sample size

The sample size was estimated based on our previous test results [18]. The sample size of this experiment was estimated by the non-inferior test. The non-inferiority margin was 6 and the standard deviation was 10.31. According to the formula, each group should have 44 participants by formulating the inspection level (0.025) and the power of test 1-β (0.2). During baseline inspection and follow-up, 50 participants in each group should participate in the experiment, given a 15% expulsion rate.

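### Stopping the exercise or relapsing counts as dropping out, and nothing in the article keeps these women in the week-12 assessment or their randomised arm; the resulting bias could go either way.

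*Protocol article*

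**What the plan says.** The Drop out criteria section of the protocol article has two entries. One is recurrence or metastasis while the intervention is running. The other is women "who cannot insist on receiving intervention for some reason", with no threshold and no restriction on the reason. Both events happen after randomisation.

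Sample size states that "The sample size of this experiment was estimated by the non-inferior test", that "The non-inferiority margin was 6 and the standard deviation was 10.31", that "each group should have 44 participants", and that "50 participants in each group should participate in the experiment", "given a 15% expulsion rate".

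Other sections bear on the point:

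- Subject grouping and Data collection and management already allow any participant to withdraw whenever she wishes. The drop-out list therefore appears to go beyond withdrawal of consent.
- Qigong group asks women who leave to give a reason. It does not ask them for an outcome measurement.
- Outcomes gives two measurement times, baseline and 12 weeks.
- Statistical analysis names a mixed-effect model and no analysis population.
- Implementation has patients "randomly divided into an experimental group and control group, with a ratio of 1:1".

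**The concern.** Stopping an exercise programme and leaving a trial are different events. The drop-out list merges them. Whether a woman keeps up her programme can depend on which programme she was given, since Baduanjin and resistance bands with walking differ in content and load. It can also depend on how well she feels, which is close to what SF-36 and FACT-B measure. Recurrence is likewise tied to quality of life, although recurrences within 12 weeks may be few, so the non-adherence entry carries most of the weight.

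If these women are not measured at week 12, the randomised groups are no longer what is compared. There is only one visit after baseline, so a woman who misses it contributes no outcome under treatment. An analysis plan can define who is analysed, but it cannot supply questionnaires that were never sought. The damage is the same in kind whether the question is non-inferiority, as in Sample size, or a plain comparison of two programmes, as in the Background and Objectives.

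**Working it through.** **Inputs from Sample size:** margin 6; SD 10.31; significance level 0.025, taken as one-sided; the 0.2 printed beside 1-β read as β, so power 0.80; 44 per group, raised to 50 for 15% loss. The scale behind the margin and SD is not named, and the assumed true difference is not stated; 0 is used here. Allocation is 1:1.

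**The plan's own figure.**

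n = 2 × [SD × (z₀.₉₇₅ + z₀.₈₀) / margin]² = 2 × [10.31 × (1.960 + 0.842) / 6]² = 46.35, so 47 per group, not 44.

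Inflating 44 for 15% loss gives 44 / 0.85 = 51.8, so 52, against the 50 stated. That 44 does not follow from its inputs is a separate issue and does not decide this one.

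**Women affected.** 0.15 × 50 = 7.5 per group, or about 15 of 100. This leaves 50 × 0.85 = 42.5 per group.

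**Power** = Φ(6 / [10.31 × √(2/n)] − 1.960):

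| n per group | Situation | Power |
|---|---|---|
| 50 | all randomised women followed | 82.9% |
| 44 | the plan's evaluable number | 77.9% |
| 43 | about 15% lost | 77.0% |
| 42 | about 15% lost | 76.0% |

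**Bias.** Let d be the share leaving an arm and g the points by which leavers would have scored below stayers. The stayers' mean exceeds the mean of all women randomised to that arm by d × g. The difference between arms (qigong minus control) is therefore biased by

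bias = d_Q × g_Q − d_C × g_C,

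which is (d_Q − d_C) × g when the gap is the same in both arms. The document gives neither d by arm nor g, so the values below are assumptions, with 15% leaving overall:

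| Leaving, qigong / control | g = 5 | g = 10 |
|---|---|---|
| 15% / 15% | 0 | 0 |
| 20% / 10% | +0.5 | +1.0 |
| 10% / 20% | −0.5 | −1.0 |

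Equal numbers are not enough by themselves. With 15% leaving each arm but a gap of 10 in qigong and 5 in control, the bias is 0.15 × 10 − 0.15 × 5 = +0.75.

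**Effect on the one-sided 2.5% error.** Suppose qigong is truly worse by exactly the margin among all randomised women. The probability of declaring non-inferiority from stayers only is Φ(bias / SE − 1.960). With 20% and 10% leaving, 40 and 45 women remain, so SE = 10.31 × √(1/40 + 1/45) = 2.24.

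- 20% qigong, 10% control: bias +0.5 gives 4.1%; +1.0 gives 6.5%; a gap of 15 (bias +1.5) gives 9.8%.
- 10% qigong, 20% control: 1.5%, 0.8% and 0.4% for the same three gaps.
- 15% in each arm with the same gap: 2.5%.

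**The case against.** The strongest reply is that exclusion is inferred, not stated. The drop-out list is two lines long and does not say that these women go unmeasured or are deleted from the analysis. The wording of the 15% allowance reads like a translation and may mean no more than expected loss. The second entry may describe women who leave of their own accord. The article is a condensed document, and an as-randomised analysis set could sit in a plan not shown. The Statistical analysis section also has a participant random effect and refers to the randomised group. If baseline is modelled as a repeated outcome, women with baseline data only can stay in the model.

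Most of this stands, and it rules out three stronger readings that a reader might infer:

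- **That the week-12 data are definitely not collected, so no as-randomised result can be recovered.** No section says so. The text creates a risk, not a certainty.
- **That the rule favours a non-inferiority conclusion.** The direction depends on which arm loses more women and how they would have scored. Leaving out non-adherers can also work against non-inferiority, because keeping them often dilutes a difference between arms.
- **That the rule is what brings power down to about 76%.** The planned 44 per group already gives only 77.9%, because 44 does not follow from the stated inputs. Ending with 42 or 43 costs a further 1 to 2 percentage points, and an allowance for 15% loss was already made.

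What does not stand is that an unseen plan settles the matter. The article states a positive rule that makes stopping the intervention a ground for dropping out, and whether such women are still assessed is a question of conduct, not only of analysis. Nor does the mixed model remove the problem. With a single visit after baseline, it must assume that women who leave resemble those who stay, given baseline. That is doubtful when the reason for leaving is relapse or inability to keep up.

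**Conclusion.** The point holds as a risk built into the drop-out rule. Two events after randomisation are made grounds for dropping out, an allowance of 15% is budgeted, and nothing in the article keeps these women in the week-12 assessment or in their assigned arm. The comparison may then rest on adherent, relapse-free women.

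The size and sign of the bias cannot be derived from the document. Under the assumed 20% against 10% split and a gap of 5 to 10 points, the bias is 0.5 to 1.0 point, or 8% to 17% of the margin (0.5/6 to 1.0/6), towards whichever arm loses more women. It vanishes only if losses are equal in number and kind. The conclusion also assumes that the points are on the unnamed scale of the margin and that leavers would score lower than stayers.

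**What to change.** 1. In Drop out criteria, separate stopping the intervention from leaving the study. Who stops the intervention, and why, need not change.
2. State that SF-36 and FACT-B will be sought at week 12 from every randomised woman who has not withdrawn consent, whatever her adherence or recurrence.
3. State that all women are analysed in the arm to which they were randomised, with a per-protocol analysis as support. Requiring the two analyses to agree before claiming non-inferiority is one convention and is not needed to repair this point.
4. In Sample size, reserve the 15% allowance for women with no week-12 questionnaire.

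The cost is a short amendment and the effort of contacting about 15 women who stopped (0.15 × 100), by telephone or online. For each questionnaire obtained, the number analysed moves back towards 50 per group.

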#### Recruiting methods

This study intends to recruit 100 subjects from Shandong province who meet the above standard through doctor recommendation or through newspapers, TV, and the Internet.Planning the recruitment schedule and confirming the source of subjectsAccording to the inclusion and exclusion criteria, carefully check the database (prescription records, medical records), medical history cards, previous trials, and local epidemiological data of the diseaseformulate the plan and method of contact with the subject, including the preparation of necessary data, videos, and pictures to help the subject understand the purpose of the test, and the design of the schemeformulate the method of obtaining the informed consent form signed by the subject or the subject’s parentsPlanning costs

### Subject grouping

Participants were briefed on the research and informed of the benefits and possible risks of clinical trials. They volunteered to participate in the study and completed an informed consent form. Subjects could withdraw from the study at any time. After the completion of informed consent, subjects were assigned to either the qigong group or the regular exercise rehabilitation group by way of a random number table. Both groups received supervised exercise twice a week and were encouraged to volunteer for 3–4 unsupervised exercise sessions per week.

### Allocation

#### Allocation concealment mechanism

The researchers who randomly assigned the sequence and determined the eligibility of the subjects were not the same person. Secondly, the research manager who generates and saves the randomly assigned sequence is the person who does not participate in the test. The treatment plan accepted by each subject was generated by the generated random distribution sequence and put into a sealed, light-tight envelope in sequence. Only when the qualified subjects agree to enter the test can the envelope be opened, and the subjects can accept the corresponding treatment measures.

### Implementation

After completing the baseline survey and physical fitness test, the computer random table generated by SPSS16.0 software was used for randomization. The eligible patients were randomly divided into an experimental group and control group, with a ratio of 1:1.

### Qigong group

Subjects in the qigong group conducted the Baduanjin through live video streaming under the guidance of professors and professionals. Baduanjin is one of the most widely circulated qigong methods, which is a traditional sport with a combination of physical activity, breathing, and psychological adjustment. The Baduanjin consists of eight movements, most of which are based on the horse stance combining movements of the upper limbs, head and neck, and spine, as well as organized breathing. In the first week, Baduanjin was taught by qualified qigong teaching staff through remote video, allowing the subjects to learn to master all movements of Baduanjin. Starting from week 2, subjects, led by a professional, performed Baduanjin twice a week, 30 min each, including 5 min of warming-up and cooling-down activities before and after the exercise. Participants were encouraged to actively practice Baduanjin during the rest of the time. Subjects were required to report their practice experience, possible adverse reactions, and side effects on a weekly basis, either orally or in writing. Subjects who exited the researcher were asked to explain the reason for the exit.

### Regular exercise rehabilitation group

The control group adopted a combination exercise of walking and resistance training [8]. Subjects underwent a 30-min resistance band training twice a week with a professional video tutorial, including 5 min of warm-up and cooling-down activities before and after the exercise. Subjects were encouraged to do walking exercise for the rest of the time, and the intensity of walking was determined based on pre-measured levels of aerobic capacity. The resistance load was determined based on the level of muscle strength measured in advance.

### Participant timeline

Figure 2 shows details on the schedule of enrollment, interventions, and assessments.

**Fig. 2 Fig2:**
[figure not shown]
Recommendations for Interventional Trials (SPIRIT) diagram of enrolment, treatment, and assessments over time

### Outcomes

All data were measured and recorded 12 weeks after the baseline and intervention. The primary outcomes are quality of life which will be evaluated by using a 36-Item Short-Form Health Survey (SF-36) and Functional Assessment of Cancer Therapy-Breast (FATC-B), and the second indicator is the level of physical fitness, including cardiopulmonary endurance, muscle strength, and flexibility.

### Quality Of Life (QOL)

#### SF-36

Sf-36 [9, 10] is a general scale for evaluating health status, and its reliability and validity have been well recognized. The questionnaire included eight dimensions: physiological function (PF), role physical (RP), bodily pain (BP), general health (GH), vitality (VT), social function (SF), role emotional (RE), and mental health (MH).

#### FACT-B (Version 4.0)

FACT-B (version 4.0) [11, 12] is a targeted scale of quality of life for breast cancer survivors. It is recognized for good reliability, validity, and reactivity. FACT-B (version 4.0) includes five dimensions: physiological well-being (7 items), social/family well-being (7 items), emotional well-being (6 items), functional well-being (7 items), and additional concerns (9 items).

### Outcomes of physical fitness

#### Cardiopulmonary endurance

Bruce scheme was adopted and a cycle ergometer was used for testing.

#### Upper-limb strength test (Dumbbell Brachiocyrtosis Test)

Subjects were asked to sit on a 44CM high-backed chair placed against the wall, hold a 5-pound dumbbell, and extend their arms to the side of the chair naturally. Then they were asked to bend their arms upward to the maximum extent, then gradually swivel them outward to the palm up, and then put their arms back to the side of the chair. The number of repetitions within 30 s was recorded.

#### Lower-limb strength test (Sitting and Standing test)

For safety, the straight-back chair (or folding chair) was placed against the wall. Subjects sat in the middle of a chair with their feet shoulder-width apart, slightly forward and backward, and crossed arms close to the chest. During the test, the subjects stood up completely, then sat down completely. The number of times the subjects sat down in a chair within 30 s was recorded. For safety or requirement, the tester can use the arm for protective assistance [13].

#### Body fat composition

The percentage of body fat will be measured by the skinfold thickness method. The measurement included the triceps, anterior suprailiac, and thigh [14]. Bring the measured data of fold thickness (mm) into the corresponding body density formula to calculate the body density value, and then bring the body density value into the Siri or Brozek prediction formula to calculate the body fat percentage.

#### Flexibility (Hand Backward Stretch Test)

The subject’s hand was curled around the ipsilateral shoulder, stretching as far as possible into the middle of the back, with the palm close to the body. Subjects put the other hand behind the back, palm outward, stretched as far up as possible, and tried to touch or overlap the middle finger of both hands. The distance between the two middle fingers was measured twice in the vertical direction with an accuracy of 0.1 cm. If the fingertips just touch, the score is zero. If they were not touched, then a negative distance is gotten, like − 5 cm/ − 2 inches; If two fingers overlap, then a positive distance is acquired, such as + 2.5 cm/ + 1 inch; Finally, the best experimental results could be acquired. When the subject is in pain during the test, the test shall stop immediately.

### Data collection and management

In order to collect data in an accurate and scientific way, we trained personnel in charge of data measurement and collection with operational specifications. During the experimental data collection process, the subject’s physical condition was closely observed and if the subject appeared any discomfort, the test would immediately stop, and the subjects would timely consult a doctor.

Monitoring was carried out by personnel independent of investigators and sponsors, including checking all informed consent and verifying the integrity of all data and source data. They would collect data and record on standard reports, and when access was complete, all recorded data were transmitted to a web-based data system through multiple inputs. All errors were crossed out with the researcher’s signature and date. Any participant could withdraw from this study at any time for any reason.

### Statistical analysis

The experimental results used mixed-effect model [15] to compare the two sets of data. The random effect of the participants was evaluated, the data were adjusted according to the random group, and the relevant baseline variables were used to analyze the data without adjusting the multiple comparisons. The effect differences between the comparison groups were calculated (expressed as effect values), and the results were expressed as inter-group differences (95% confidence intervals). All analyses were performed using Stata 13.1 or the updated version.

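### With two primary instruments, no adjustment, no success rule and one unlabelled margin, the stated one-sided 0.025 and the planned 80% power cannot both hold for the primary claim

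*Protocol article*

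**What the plan says.** All of this is in the protocol article.

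- **Outcomes** (and the Abstract): quality of life is primary, "evaluated by using a 36-Item Short-Form Health Survey (SF-36) and Functional Assessment of Cancer Therapy-Breast (FATC-B"). The two instruments are listed side by side with no order between them.
- **SF-36**: "The questionnaire included eight dimensions". No total or summary score is named.
- **FACT-B (Version 4.0)**: "FACT-B (version 4.0) includes five dimensions", of 6, 7 or 9 items each. Again no total is named.
- **Statistical analysis**: "the relevant baseline variables were used to analyze the data without adjusting the multiple comparisons", and "the results were expressed as inter-group differences (95% confidence intervals"). The no-adjustment statement is not limited to secondary outcomes.
- **Sample size**: "The sample size of this experiment was estimated by the non-inferior test". "The non-inferiority margin was 6 and the standard deviation was 10.31". The level is 0.025. The power entry is printed as 1-β (0.2), which we read as β = 0.2, so 80% power. The result is 44 per group, raised to 50 for 15% loss. The section refers to the team's own previous study but names no instrument, score or unit.

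No section says whether success on one instrument is enough or both are needed.

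**The concern.** The sample size section describes one comparison on one score. The outcomes section describes two instruments of equal rank. Nothing connects them, and the analysis section rules out the usual way of keeping the overall error at its stated level.

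Two things are at stake. First, the error rate and power of the primary claim depend on a decision rule that is not written, so the rule could be settled after the results are known. Second, a margin of 6 raw points has no meaning until its scale is named. The same 6 points cannot mean the same thing on an eight-dimension generic scale and on a FACT-B score built from 6, 7, 9 or all 36 items. As written, nobody can tell which confidence limit is to be compared with 6, or judge whether 6 is acceptable.

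**Working it through.** **Inputs.** From Sample size: margin 6, SD 10.31, one-sided level 0.025, power read as 0.80, 44 per group. From Outcomes: two primary instruments. From the two instrument sections: 8 + 5 = 13 dimension scores. Assumptions not in the document: true difference 0; for joint power, the same margin-to-SD ratio on both instruments; correlation between test statistics varied from 0 to 0.9.

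**1. The plan's own figure, one test.**
n per group = 2 × [10.31 × (1.960 + 0.842) / 6]² = 46.35, so 47. The stated 44 is not reproduced. This is a separate matter, but it sets the baseline. At 44 per group:
- standard error = 10.31 × √(2/44) = 2.198
- 6 / 2.198 = 2.730
- power = Φ(2.730 − 1.960) = Φ(0.770) = 0.779

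A single test therefore has about 78% power, not 80%, before multiplicity enters.

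**2. Either instrument suffices.** Each test is at one-sided 0.025, matching one limit of a 95% interval. The null is the least favourable one: the true difference on each instrument lies exactly at its margin.
- Independent: 1 − 0.975² = 0.0494
- Correlated: 1 − P(both statistics below 1.960), bivariate normal

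| Correlation | Chance of a false claim |
|---|---|
| 0 | 4.9% |
| 0.5 | 4.5% |
| 0.7 | 4.2% |
| 0.9 | 3.5% |

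The stated level is 2.5%.

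**3. Both instruments must succeed.** Alpha stays at 0.025 with no adjustment. Joint power at 44 per group is P(both standard normals below 0.770):

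| Correlation | Joint power |
|---|---|
| 0 | 61% (0.779² = 0.607) |
| 0.5 | 66% |
| 0.7 | 69% |
| 0.9 | 73% |

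The fair comparison is with the 78% of step 1. The gap from 78% to 80% belongs to the sample size itself and not to multiplicity.

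**4. Worst case only: any of the 13 dimension scores could support the claim.**
- Independent: 1 − 0.975¹³ = 0.280
- Equicorrelated normal statistics: 17% at 0.5, 12% at 0.7, 7% at 0.9

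**5. Price of splitting alpha between two primaries.** At 0.0125 each, n = 2 × [10.31 × (2.241 + 0.842) / 6]² gives 57 evaluable per group, and 57 / 0.85 gives 68 enrolled. At 44 per group, each such test would have 69% power.

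**The case against.** The strongest reply has three parts.

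*The success rule and the choice of score may be in the full protocol or the SAP.* Partly right. A condensed article may leave scoring detail elsewhere, and the previous study cited for the sample size may identify the score. But the refusal to adjust is a stated decision, applied without restriction to a design with two primaries. The margin is printed as a raw number without its scale. A later document that simply followed this text would inherit both problems.

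*Co-primary endpoints need no adjustment.* True if both must succeed. The article does not say so, and under that rule the sample size is too small for the power it claims.

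*The design may be exploratory.* The sample size section sets a margin, a level and a power, and the Discussion describes the sample as sufficient to verify the effect. That is confirmatory language.

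Two stronger readings are tempting and should not be adopted. A reader might infer that 13 primary tests are planned, because the dimensions are the only scores described. The article lists them as the contents of the questionnaires and does not declare them as endpoints, so 7% to 28% is an outer bound. The 28% end also needs 13 independent scores, which is unlikely for subscales completed by the same patient. A reader might also infer that the error rate certainly exceeds 0.025. It does so only under an either-suffices rule; with no rule written, the rate is undefined. Two-sided error figures would not fit a one-sided non-inferiority test, because they also count results favouring the control.

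**Conclusion.** The point holds for two instruments. Under an either-suffices rule the false-claim rate is 3.5% to 4.9% instead of 2.5%. Under a both-required rule the level holds, but joint power at 44 per group is about 61% to 73%, against about 78% for one test and the planned 80%. Unless the two test statistics are almost perfectly correlated, neither rule delivers both stated figures.

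The error figures rest on normal test statistics and a true difference at the margin on each instrument. The power figures rest on a true difference of 0 and an equal margin-to-SD ratio on both, which the article neither states nor contradicts. The missing label on the margin and SD needs no assumption; it is plain from the text.

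This should be settled before any outcome data are analysed, since the score, its margin and the decision rule together define what the trial can claim.

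**What to change.** 1. Name as the single primary outcome the score from which the SD of 10.31 and the margin of 6 were taken, and write that score's name beside both figures in the sample size section. The sponsor has to supply it; the article does not show whether it is an SF-36 or a FACT-B score.
2. Test the other instrument second in a fixed sequence, at the same one-sided 0.025, only if the first succeeds. Name its score and give it a margin on its own scale. If no margin can be justified, make it a superiority test or report it descriptively.
3. Make all other dimension scores secondary.
4. Limit the no-adjustment statement to secondary outcomes.

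**Cost:** wording, plus a justified margin for the second instrument if it is to be tested for non-inferiority. This change needs no extra patients or data. The downside is that the second instrument loses its stand-alone primary status.

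If the sponsor wants to keep both as primary, a both-required rule or a split alpha is also valid, but the trial must then be resized. Splitting alpha would need 57 evaluable and 68 enrolled per group under the assumptions above. The shortfall of 44 against 47 for a single test should be corrected separately.
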